### Methods for additional analyses (e.g., subgroup analyses) {20b}

Subgroup analyses will be conducted to evaluate the effects of the intervention within predefined groups, such as age (categorized into ≤35 years and >35 years), embryo quality, and cause of infertility. These analyses will help determine if the efficacy of the direct warming method varies across these specific subgroups compared to the conventional multi-step method.

Adjusted analyses will be performed using logistic regression to control for potential confounders, including maternal age, previous IVF cycles, and embryo grading. These adjusted analyses will provide more accurate estimates of the treatment effect on the primary and secondary outcomes.

No additional exploratory analyses are currently planned, though further analyses may be considered based on emerging data trends during the study.

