### Sample size {14}

The sample size calculation was based on preliminary data indicating approximately a 5% increase in the live birth rate with the new method compared to conventional warming. With type I error (*α*) set at 0.05 and type II error (*β*) set at 0.2 (80% power), and assuming a clinically significant difference of 20% in the worldwide clinical pregnancy rate, the required sample size per arm is 275, calculated using MedCalc 15.6.1. To account for a 5% loss to follow-up, a total of 578 participants will be enrolled (289 per arm). Given that the total number of participating centers is currently undetermined, the leading center, IVFHK-CUHK, will serve as the core recruitment site. This center can independently recruit at least 578 participants.

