## Statistical methods

### Statistical methods for primary and secondary outcomes {20a}

All analyses will follow an intention-to-treat (ITT) approach, with statistical significance set at *p* < 0.05 and 95% confidence intervals (CI). Primary outcomes, including embryo survival rate, pregnancy rate, clinical pregnancy rate, and live birth rate, will be analyzed using logistic regression models, adjusting for potential confounders such as cause of infertility, previous ART cycle, and embryo quality. Chi-square tests or Fisher’s exact tests will be used for categorical outcomes like embryo survival, and logistic regression will report odds ratios (OR) for pregnancy and live birth rates.

Secondary outcomes, including implantation rate and multiple gestation pregnancy rate, will be analyzed using generalized linear models (GLM) and chi-square tests. Thawing time will be compared using *t*-tests or Mann-Whitney *U* tests for non-normal data. Cost-effectiveness will be evaluated through cost-effectiveness analysis (CEA), while post-thaw embryo quality will be assessed using standard grading criteria and analyzed with chi-square tests. Missing data will be handled using multiple imputation to maintain the integrity of the results. An extra sensitivity analysis will be conducted if loss to follow-up is more than 5%.

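### Section {20b} says that effects within each subgroup will show whether efficacy varies between subgroups, but separate within-group effects do not test that difference

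*Protocol article*

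**What the plan says.** Methods for additional analyses {20b} gives a method and then the conclusion to be drawn from it.

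- The method: "Subgroup analyses will be conducted to evaluate the effects of the intervention within predefined groups", the groups being "such as age (categorized into ≤35 years and >35 years), embryo quality, and cause of infertility".
- The conclusion: "These analyses will help determine if the efficacy of the direct warming method varies across these specific subgroups".

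The section also plans logistic regression, but only to adjust for confounders (maternal age, previous cycles, embryo grading). Statistical methods {20a} sets a 5% significance level with 95% confidence intervals for all analyses, and reports odds ratios from logistic models. None of {20a}, {20b} or {20c} mentions a treatment-by-subgroup term or any other direct comparison of subgroup effects. None of them says what result would count as evidence that efficacy varies.

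**The concern.** Whether efficacy varies is a question about the difference between two subgroup effects. Estimating each effect on its own, with its own p-value, answers another question: whether there is an effect in that group. Two subgroups can share the same true effect and still fall on opposite sides of 5%, because each holds only part of the sample.

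At stake is a chance finding that direct warming works, or fails, in one age group or for one cause of infertility. Such a finding could influence how laboratories choose a warming method for those patients. Subgroup comparisons carry some weight here, since the Abstract also assigns the secondary questions on media brands and storage devices to subgroup analyses.

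**Working it through.** **Inputs from the protocol article**

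- Significance level 0.05 ({20a}), taken as two-sided because sidedness is not stated.
- Power 80% and 275 per arm (Sample size {14}).
- Two effect sizes in {14}: "approximately a 5% increase in the live birth rate with the new method compared to conventional warming" and "assuming a clinically significant difference of 20% in the worldwide clinical pregnancy rate".
- Age has two levels. The levels of the other two factors are not given.

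**Assumptions**

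- One factor with two equal halves and the same true effect in both.
- Variation is declared when exactly one half is significant. The protocol does not state this rule; it is used to size the risk of the most natural misreading.

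**The plan's own figure.** {14} states "the required sample size per arm is 275, calculated using MedCalc 15.6.1". No baseline rate is given, and the 20% is not said to be absolute or relative, so 275 cannot be reproduced from the stated inputs. An absolute 20-point difference needs 82 to 97 per arm (baseline 20% to 60%). A 20% relative increase needs 282 per arm from 57% and 269 from 58%, so 275 fits an assumed baseline near 58%. The first case below needs only the 80% power, not the baseline.

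**Case 1: effect giving 80% overall power**

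- Expected overall z-statistic: 1.96 + 0.84 = 2.80.
- In a subgroup with share s it is 2.80 × √s. With s = 0.5 it is 2.80/√2 = 1.98.
- Power in each half: Φ(1.98 − 1.96), which is 0.508 with unrounded values.
- Exactly one half significant: 2 × 0.508 × 0.492 = 0.50.
- Unequal splits, using p₁(1 − p₂) + p₂(1 − p₁): 40:60 gives 0.425 × 0.417 + 0.583 × 0.575 = 0.51; 30:70 gives 0.55.

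**Case 2: 5-point effect**

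The preliminary 5% is read as 5 percentage points, with an assumed baseline of 30% to 50% and about 137 per arm in each half.

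- Expected z = 0.05 / √{[p₀(1 − p₀) + p₁(1 − p₁)]/n}.
- Baseline 30%: 0.05/√[(0.2100 + 0.2275)/137] = 0.885. Power = Φ(0.885 − 1.96) = 0.141. Exactly one significant: 2 × 0.141 × 0.859 = 0.24.
- Baseline 45%: 0.05/√[(0.2475 + 0.2500)/137] = 0.830. Power = 0.129. Exactly one significant: 2 × 0.129 × 0.871 = 0.22.
- Overall power with 275 per arm is 22% to 24% over the same baselines.
- These figures ignore significance in the wrong direction; including it raises the rate by less than half a percentage point.

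**Case 3: no treatment effect**

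- Exactly one significant: 2 × 0.05 × 0.95 = 0.095.

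**Check by simulation** (200,000 runs, Wald tests on the log odds ratio, 275 per arm, equal halves)

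| True rates, control vs direct | Exactly one half significant | Interaction test significant |
|---|---|---|
| 48% vs 60% | 50.0% | 5.0% |
| 45% vs 50% | 22.2% | 4.8% |
| 40% vs 45% | 22.2% | 5.0% |
| 45% vs 45% | 8.8% | 4.9% |
| 40% vs 40% | 9.2% | 5.1% |

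The interaction test stays near 5% whatever the size of the common effect.

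**The case against.** The best counter-argument is that this is under-specification, not error. Only a journal article is at hand, and the choice of heterogeneity test is commonly left to the analysis plan or the full protocol. Reporting within-group effects is compatible with an interaction test, and the section excludes none. It calls these additional analyses, the age cut-point matches the randomization strata, and odds ratios with 95% confidence intervals are already planned.

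Much of this stands. A reader might infer that the trial has no interaction test at all; the article does not show that, and its silence would not be a finding. A reader might also infer that the plan will produce false subgroup differences half the time. The documents do not support that either. They state no rule based on significance in one group and not the other, and the 50% also requires a common effect as large as the one giving 80% power. Nor should the harm be pressed for poor embryos: eligibility requires at least one good-quality blastocyst, defined as 3BB or better, so the embryo-quality subgroups probably lie mostly within that range.

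The counter-argument does not remove the link between the two sentences. The section names a method and says what it will help determine, and the method as described does not test that. An interaction test in another document would leave the published description wrong.

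**Conclusion.** The point holds in this limited form: {20b} draws a conclusion about variation between subgroups from analyses described only as within-subgroup. The size of the risk is conditional. If variation were read from one subgroup being significant and the other not, a single two-level, equally split factor with the same true effect in both levels would give a false signal in about 10% of trials with no treatment effect, 22% to 24% with a 5-point effect and about 50% with an effect giving 80% overall power. An interaction test gives about 5%. The range rests on a reading rule that the protocol does not state and, for the middle figure, on an assumed baseline of 30% to 50%. The primary comparison is untouched. The wording should be corrected, but this is not a flaw that threatens the trial's main result.

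**What to change.** In {20b}, state that variation of the treatment effect is assessed by a treatment-by-subgroup interaction term in the logistic model already planned, fitted for age stratum, embryo quality and cause of infertility, each reported with its 95% confidence interval. Show within-subgroup odds ratios with 95% confidence intervals as descriptive only, and draw no conclusion from within-subgroup p-values. If another document already specifies this, align the published wording with it.

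The cost is a sentence or two, plus one interaction per factor (several coefficients where a factor has more than two levels). No further participants or data are needed. The drawback is that interaction tests have low power at this sample size, so a non-significant interaction will not show that the effect is uniform. The text should say so.

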### Methods in analysis to handle protocol non-adherence and any statistical methods to handle missing data {20c}

The primary analysis will be conducted on an ITT basis, which includes all participants as randomized, regardless of protocol adherence or deviations. Participants who discontinue the intervention will still be analyzed in the group to which they were originally assigned to preserve the randomization process.

To address potential missing data, multiple imputation techniques will be employed. Missing values will be imputed based on available baseline and follow-up data, ensuring that the analysis maintains sufficient statistical power. Sensitivity analyses will also be performed to assess the robustness of the results, comparing complete case analyses to those using imputed data.

Per-protocol analyses may also be conducted as a secondary analysis to assess the outcomes among participants who fully adhered to the study protocol.

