### Trial design {8}

This is a two-arm, double-blinded, parallel-group, multi-center, randomized controlled trial (RCT) with a superiority framework. The trial will compare the efficacy and safety of the new direct warming method against the conventional multi-step warming method for FET.

Participants will be randomized in a 1:1 allocation ratio into one of two groups:Intervention (arm 1): the new direct warming method.Control (arm 2): standard care using the conventional multi-step warming method.

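### At or below the planned 5% loss, the only missing-data sensitivity check in force is complete case against multiple imputation, which cannot show robustness to informative loss of live-birth data

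*Protocol article*

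**What the plan says.** Three sections of the protocol article bear on this.

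- **Section {20c}, non-adherence and missing data.** The main analysis is by intention to treat with multiple imputation: "Missing values will be imputed based on available baseline and follow-up data, ensuring that the analysis maintains sufficient statistical power". The robustness check follows: "Sensitivity analyses will also be performed to assess the robustness of the results, comparing complete case analyses to those using imputed data".
- **Section {20a}, statistical methods.** Multiple imputation is repeated, and a conditional step is added: "An extra sensitivity analysis will be conducted if loss to follow-up is more than 5" per cent. No method is given for it.
- **Section {14}, sample size.** The planned loss is 5%, which takes 275 per arm to 289. The same paragraph cites preliminary data showing "approximately a 5% increase in the live birth rate with the new method compared to conventional warming", without a control rate and without saying whether the increase is absolute or relative.

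Live birth is one of the primary outcomes in section {12}, defined as a proportion of participants. Table 1 sets out how it is reached: hCG test at 10–14 days, ultrasound at 6–8 weeks, then telephone contact at 20–24 weeks, at 36–40 weeks and after birth.

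**The concern.** A sensitivity analysis for missing data should vary the assumption that the main analysis cannot verify. Here that assumption is that, given what was observed, participants with an unknown live-birth outcome resemble those with a known one. Comparing complete case with imputed results does not vary it in the direction that matters. Neither analysis lets an unseen outcome differ from the seen ones because it is unseen.

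Complete case is also a weak comparator for this outcome. A negative test settles live birth within two weeks of transfer, whereas a pregnant participant must be followed to delivery, largely by telephone. Late loss therefore removes pregnancies, and complete case drops them.

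The 5% trigger compounds this. If loss stays within the plan, nothing else is required. A conclusion on live birth could then be called robust on a comparison that did not test it.

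**Working it through.** **1. The planned loss.** Section {14}: 275 × 1.05 = 288.75, rounded to 289 per arm and 578 in total, as printed. (Dividing instead, 275 / 0.95 = 289.5, gives 290 per arm; the difference is immaterial here.) Planned loss per arm is 289 − 275 = 14, and 14 / 289 = 4.8%. This is under 5%, so the conditional analysis in {20a} would not start.

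**2. What each analysis assumes.**
- Multiple imputation from baseline and follow-up data: loss may depend on anything observed and used in the model, but not on the unseen outcome beyond that.
- Complete case: loss must be unrelated to outcome given arm and the model covariates alone. It cannot use pregnancy status after transfer, so its assumption is stronger.

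If loss is informative beyond the observed data, both can be wrong together. If loss depends on pregnancy status, they can differ although the imputation is sound.

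**3. Size of complete-case bias (assumed figures).** Take a true live-birth rate of 40% in one arm, with 14 lost, all pregnant, of whom 80% deliver.
- True births: 0.40 × 289 = 115.6
- Births among those lost: 0.80 × 14 = 11.2
- Complete case: (115.6 − 11.2) / 275 = 104.4 / 275 = 38.0%

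That is 2 points too low. Equal loss in both arms would largely cancel in the difference; loss in one arm only would create a spurious 2 points.

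**4. Limits for the live-birth difference.** Assumed observed rates are 45% (direct) and 40% (conventional), with 275 observed and 14 lost per arm. Observed births: 0.45 × 275 = 123.75 and 0.40 × 275 = 110.

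| Assumption about the 14 lost per arm | Difference |
|---|---|
| None deliver in direct arm, all in control arm | (123.75 − 124) / 289 = −0.1 points |
| All deliver in direct arm, none in control arm | (137.75 − 110) / 289 = +9.6 points |
| None deliver in either arm | (123.75 − 110) / 289 = +4.8 points |
| Direct 20 points worse (25%), control 20 points better (60%) than observed | (127.25 − 118.40) / 289 = +3.1 points |

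With control rates of 30%, 40% and 50%, 14 or 15 lost per arm, a gain of about 5 points and whole births, the lower limit is 0.0 to −0.7 points and the upper +9.3 to +10.0. The opposite 20-point departures leave 2.7 to 3.2 points.

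**5. If the 5% gain is relative.** With a 40% control rate the direct rate is 42%, a gain of 2 points. Observed births in the direct arm: 0.42 × 275 = 115.5.
- Limits: (115.5 − 124) / 289 = −2.9 and (129.5 − 110) / 289 = +6.7 points
- Opposite 20-point departures (22% and 60%): (118.58 − 118.40) / 289 = +0.1 points

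**The case against.** **The choice of sensitivity analysis belongs in the analysis plan, which is not shown.** This is largely right: the absence of a tipping-point analysis from a condensed article is not an error. What stands is narrower. The article itself commits to one comparison as its test of robustness and to a 5% threshold for anything more, and both choices are poor.

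**A reader might infer that this is the only missing-data check in the plan.** It is not. Section {20a} promises another above 5% loss. The point holds only at or below 5%.

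**A reader might infer that the check passes by construction.** The article does not support that. Imputation from follow-up data may use the hCG and ultrasound results, and the result could then differ from complete case. The comparison can reveal dependence of loss on observed pregnancy status; it cannot address dependence on the unseen outcome.

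**A reader might infer that the planned loss is as large as the expected effect.** The two 5% figures share a paragraph, but the gain may be relative, and cancelling a 5-point gain takes every loss going in opposite directions in the two arms. Section {17a} blinds participants, clinical team and outcome assessors, {16b} keeps pregnant participants unaware of their arm until birth or loss, and {18b} plans recovery from medical records. Strongly opposite losses are unlikely.

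**Sampling error dominates.** At 45% and 40% with 289 per arm, the standard error is √[(0.45 × 0.55 + 0.40 × 0.60) / 289] = 4.1 points, so z is about 1.2. A 5-point difference would not be significant even with complete data. This stands, and it limits the consequence.

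**Not all loss is late.** Withdrawal is allowed at any time, so some outcomes may be lost before any test. That is why the point says mainly, not wholly, among pregnant participants.

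**Conclusion.** The concern holds in a limited form and is minor. Within the planned loss, the one check in force cannot show that a live-birth result is robust to informative loss, and a discrepancy between its two analyses would be hard to interpret. The intention-to-treat principle and multiple imputation are not at fault.

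The range from −0.1 to +9.6 points is a limit for 14 of 289 lost per arm. It rests on assumed rates of 45% and 40% and on reading the gain as absolute. Large but less extreme opposite departures, 20 points in each arm, leave about 3 points on that reading; if the gain is relative with a 40% control rate, they leave almost nothing. That losses fall mainly among pregnant participants is inferred from the follow-up schedule in Table 1; the article does not state it.

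**What to change.** 1. Keep multiple imputation as the main analysis. State that the model includes arm and last known pregnancy status, and that participants with a confirmed negative test or no gestational sac count as having no live birth.
2. Replace or supplement the complete-case comparison in {20c} with a delta-adjusted (tipping-point) analysis of live birth, with the departure varied separately by arm, and report best-case and worst-case bounds.
3. Remove the 5% trigger in {20a}, so that this analysis runs whatever the loss.

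The cost is a little extra analysis and a few lines of text. No new data are needed, and neither the sample size nor the follow-up schedule changes.

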### Plans to give access to the full protocol, participant-level data, and statistical code {31c}

The full study protocol, participant-level datasets, and statistical code will be made available upon reasonable request to the principal investigator after the study’s conclusion and publication of the main findings. Access to data will be granted in accordance with applicable institutional and regulatory guidelines, ensuring the protection of participant confidentiality.

Data sharing requests will be evaluated on a case-by-case basis, and appropriate data-sharing agreements will be required. Anonymized participant-level data will be provided to ensure that no personal identifiers are shared.

There are no plans for public data repositories or direct public access to the full dataset or statistical code at this time.

## Oversight and monitoring

### Composition of the coordinating center and trial steering committee {5d}

The coordinating center for this trial is based at IVFHK-CUHK, which will oversee the day-to-day management of the study across all participating sites, including CUHK Medical Centre and the HEAL Fertility. The coordinating center is responsible for protocol implementation, site coordination, data collection, monitoring, and regulatory compliance. It will provide logistical and administrative support to ensure adherence to study procedures and timelines. It consists of a trial manager (oversee the entire trial operation, monitor performance indicators, and communicate with other bodies), regulatory specialist (manage and monitor all regulatory documents including ethics application and renewal, protocol amendments, and other reports), site coordinators (communicate with individual centers, especially about the standard procedures), research nurses (provide clinical oversight and review medical records of the participants), and data coordinators (data collection, entry, and storage). The coordinating center will hold regular meetings (at least quarterly) to review trial progress and address operational challenges.

The TSC will provide oversight, ensuring the trial adheres to the study protocol and relevant regulations. The TSC will meet biannually to assess study progress, review interim data if needed, and discuss any protocol deviations or necessary amendments. The TSC comprises an independent chairperson, clinical experts in obstetrics and gynecology, a statistician, an ethics advisor, and the principal investigator. Most members are independent, ensuring objective oversight of the trial.

The Data Management Team, integrated within the coordinating center, will oversee data entry, coding, and storage, ensuring the accuracy and security of the data.

No additional committees, such as an endpoint adjudication committee or data monitoring committee, are planned. The study team and the TSC will collectively handle oversight of key outcomes and adjudication, as needed.

### Composition of the data monitoring committee, its role and reporting structure {21a}

Given the low-risk nature of the intervention and the multi-center design of this study, a formal DMC will not be established. Instead, oversight of safety monitoring and interim analyses will be managed by the TSC. Oversight and decision-making responsibilities, particularly those related to safety and data integrity, are adequately covered by the TSC.

